### 2. COST EFFECTIVENESS ANALYSIS (CEA)

#### 2.1. General considerations

A cost-effectiveness analysis will be performed comparing costs and effects of "BETER care" versus "no BETER care". The analysis will be performed from a healthcare and societal perspective of the Netherlands, using a 5-year (based on data from the current study) and long term/lifetime (based on extrapolations by means of data from literature) time horizon. In the study, we will derive information on proportions- and types of late effects occurred in an early or late stage after their initial treatment. We expect that screening will either find late effects in an earlier stage (which will presumably lead to lower healthcare costs and complaints, and higher QoL), or even will prevent late effects from occurring.

#### 2.2. Cost analysis

Direct and indirect healthcare costs will be gathered in the proposed study, extracted via patient files (direct healthcare consumption), and productivity losses via the questionnaires (indirect costs), as described above. Benchmark costs from the Dutch NZA or costs from the handbook of costing studies from the Dutch Zorginstituut will be used if possible; otherwise, an Activity Based Costing method will be performed for health care consumption which is unknown.

#### 2.3. Patient outcome analysis

Effects will be expressed in costs/DALYs and costs/QALYs obtained from the proposed study, and additional literature. For the DALYs, we will use the incidence/prevalence, frequency and severity of morbidities in the study to obtain the years less lived (YLL). To calculate the years lived with disease (YLD), we will use disease weight based on literature (18–21,28). For the QALYs, we will use utilities by means of the EQ-5D-5L for both intervention and control groups at the end of follow-up in 2021-2024. Long term consequences can be partly based on the current study, in combination with additional literature to extrapolate the effects for life time.

#### 2.4. Cost-effectiveness Analysis

The cost-effectiveness analysis will be performed by means of a discrete event simulation, to take the factor "timing" into account and because patient level data is available. In the cost-effectiveness analysis, we will incorporate several scenarios for follow-up strategies, based on the data generated in the proposed study. The results of the cost-effectiveness analysis will be incremental costs (or savings) of the BETER care per QALY gained. The CEA will be performed according to the guidelines for economic evaluations of the Dutch Zorg Instituut. State of the art health economic methods will be applied. Uncertainty around the results will be quantified by means of non-parametric bootstrapping and cost-effectiveness acceptability curves, showing the possibility of the BETER care being whether or not cost-effective for various values of the Dutch society willingness to pay for one QALY.

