#### 8.5. Study design (s):

8.5.1. De commissie vraagt zich af of u sterfte kunt meten, omdat het matching protocol alleen patiënten kan selecteren die zich aanmelden én dus nog in leven zijn. De commissie vraagt u dit punt te verduidelijken.

For the conduct of the study, we use a previously established comprehensive data set from a large nationwide retrospective cohort of all lymphoma survivors treated in 27 BETER centres between 1965 and 2012, with patient characteristics, treatment data, and outcome including date and cause of death. This allows selection of a control population of individuals who were not yet screened during 2013-2016, yet alive at the time the corresponding survivor in the intervention group was invited to come to the BETER clinic. Matched controls eligible for BETER screening in 2013-2016 who died during follow-up, prior to invitation for BETER screening in a BETER clinic 2021-2024, are eligible for our study. Date and cause of death are also known for survivors who were invited to attend a BETER clinic (regardless of whether they attended or not). This way mortality rates can be assessed for both the intervention and the control group.

8.5.2. De commissie merkt op dat uw aanvraag onvoldoende informatie bevat over de uit te voeren analyses van klinische effecten en kosteneffectiviteitsanalyse. U dient de geplande analyses nader toe te lichten in uw subsidieaanvraag.

We have elaborated on the subject in paragraph '2. COST EFFECTIVENESS ANALYSIS (CEA)'.

8.5.3. U dient nader toe te lichten hoe de matching plaatsvindt.

We have elaborated on this subject in paragraph '1.2.3. Control group'

8.5.4. Voor de kosteneffectiviteitsanalyse wordt gebruik gemaakt van een DES model, maar het is de commissie niet duidelijk waar de data voor dit model vandaan komen. De commissie verzoekt u dit nader toe te lichten.

We have further elaborated on this subject in paragraph '2.5. Cost-effectiveness Analysis'. The cost-effectiveness analysis will be performed by means of a discrete event simulation, to take the factor "timing" into account and because patient level data is available. We will perform an analysis on the 5-year data, based on the study. In addition, we will estimate the long term effects by means of a discrete event simulation, based on the study data, combined with extrapolations with data from e.g. literature.

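### Section 2.4 names patient bootstrapping for the cost-effectiveness results without separating the lifetime model; applied there, it leaves out the uncertainty of the literature inputs

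*Protocol*

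**What the plan says.** Section 2.4 fixes the model type: "The cost-effectiveness analysis will be performed by means of a discrete event simulation". It then gives one statement on uncertainty, "Uncertainty around the results will be quantified by means of non-parametric bootstrapping and cost-effectiveness acceptability curves", with the curves drawn over willingness to pay per QALY.

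The plan has two horizons. Section 2.1 sets a 5-year horizon based on study data and a "long term/lifetime (based on extrapolations by means of data from literature) time horizon". Section 2.3 says that long-term consequences can be based partly on the study, "in combination with additional literature to extrapolate the effects for life time". The reply at 8.5.4 repeats that the long-term model is "based on the study data, combined with extrapolations with data from e.g. literature". For the DALY outcome, section 2.3 adds "we will use disease weight based on literature".

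Two other statements in section 2.4 bear on the point. On scenarios: "we will incorporate several scenarios for follow-up strategies, based on the data generated in the proposed study". On standards: "The CEA will be performed according to the guidelines for economic evaluations of the Dutch Zorg Instituut", followed by a general promise of up-to-date health economic methods. The protocol nowhere describes a probabilistic or deterministic sensitivity analysis of the literature inputs.

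**The concern.** A non-parametric bootstrap reproduces the sampling error of the records that are resampled. An input taken from a publication has no patient records in this study, so it has the same value in every replicate and contributes no variance. A lifetime acceptability curve built this way shows how probable it is that BETER care is cost-effective if every literature input is exactly right. Section 2.4 presents the curve as the answer to the unconditional question.

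The protocol itself indicates that such inputs matter. Section 4.3.2 reports that an earlier lipid-screening model in Hodgkin lymphoma survivors was very sensitive to the assumed cardiovascular risk increase and statin efficacy. Section 4.3.5 says that an echocardiography-screening model was most sensitive to assumed treatment efficacy. Section 1.8 and the cost-effectiveness sections supply no other safeguard, and the implementation section says the results will inform adoption, adaptation or de-implementation of the guidelines. Overstated certainty in either direction could therefore affect decisions.

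**Working it through.** **Which inputs the bootstrap varies**

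| Input | Source in the protocol | Varies when study patients are resampled? |
|---|---|---|
| Events, deaths and care use during follow-up | Study (1.6.1.1, 2.2) | Yes |
| EQ-5D-5L utilities at end of follow-up | Study (2.3) | Yes |
| Post-study effects and risks | Partly study, partly literature (2.1, 2.3, 8.5.4) | Study part yes, literature part no |
| Disability weights | Literature (1.6.1.2, 2.3) | No; they enter cost/DALY only |
| Unit prices | Tariffs, benchmark prices, costing manual (2.2) | No, but these are set prices, not estimates with sampling error |

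The protocol does not itemise the literature inputs. A lifetime extrapolation would need at least the duration of effect and the event and mortality risks after follow-up. The scenarios in 2.4 vary follow-up strategies using study data, so they do not test these inputs.

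**Precision borrowed for illustration.** The protocol states no cost-effectiveness ratio, interval or probability, so there is no figure of that kind to reproduce. Section 1.7.2 gives 393 per arm for 0.20 SD: n = 2 × (1.960 + 0.842)² / 0.20² = 392.4, so 393, as stated. Treating the expected 0.40 DALY (section 1.7.1) as 0.20 SD gives SD = 2.0. This SD is an assumption. Then SE = 2.0 × √(2/393) = 0.143 and effect/SE = 0.40/0.143 = 2.80.

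**Case A: literature as a multiplier on the study effect.** This case is closer to section 2.3, which bases long-term consequences partly on the study. Ratio of true spread to bootstrap-only spread = √(1 + (0.40 × CV/SE)² + CV²):

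| CV of multiplier | 0.1 | 0.2 | 0.3 | 0.5 |
|---|---|---|---|---|
| SD 2.0 (SE 0.143) | 1.04 | 1.16 | 1.34 | 1.79 |
| SD 3.0 (SE 0.214) | 1.02 | 1.09 | 1.19 | 1.46 |

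False readings: set the true net benefit to zero, and count a reading as false when the bootstrap probability of being cost-effective is at least 95%. In SE units the study estimate is d ~ N(2.80, 1) and the cost offset is 2.80. With an estimated multiplier m, the reading occurs when m·d − 2.80 > 1.645·m. Given m, its probability is Φ(2.80 − 1.645 − 2.80/m) = Φ(1.155 − 2.80/m), which equals 5% at m = 1. Averaging over a log-normal m with mean 1 gives 5.3%, 6.2%, 7.2%, 9.0% and 9.6% for CV 0.1, 0.2, 0.3, 0.5 and 0.6. A normal m gives 5.4% at CV 0.1 and 11.4% at CV 0.6. A separate simulation of the multiplier case gave 5.9% at CV 0.1 and 10.2% at CV 0.6, which agrees with the log-normal figures within simulation error. The rate rises less than the spread because a high m also widens the bootstrap interval.

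Effect on the curve itself (SD 2.0):
- Incremental cost equal to half the expected monetised benefit: the bootstrap-only probability is 0.92. With CV 0.2, 0.3 and 0.5 it is 0.90, 0.88 and 0.80.
- Incremental cost of zero: it stays at 0.998 throughout.

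**Case B: literature supplies the post-study benefit independently.** Assume 8 years observed (the expected median follow-up in 1.5) out of an assumed horizon H, with study weight w = 8/H. The ratio of literature variance to study variance is r = [(1 − w) × CV / (w/2.80)]², and the false-reading rate is P(Z > 1.645/√(1 + r)).
- H = 20, CV 0.2: r = (0.6 × 0.2 / 0.1429)² = 0.71, rate 10.4%.
- H = 30, CV 0.2: r = (0.733 × 0.2 / 0.0952)² = 2.37, rate 18.5%.
- Over CV 0.1–0.5, simulation gave 7–25% (H = 20) and 9–34% (H = 30). Drawing the literature inputs as well brought this to 4–6%.
- The rate doubles to 10% once r reaches (1.645/1.282)² − 1 = 0.65.

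**The case against.** The strongest reply is that section 2.4 does not say bootstrapping is the sole method. It commits the analysis to the Dutch guidelines and to up-to-date methods, 8.5.4 treats the 5-year and long-term analyses separately, and distributions and replicate counts commonly belong in an analysis plan that is not shown. Part of this stands. A reader might infer that the protocol excludes any other method, and the text does not say so. The guideline's content is not in the documents, so it can neither supply nor rule out a probabilistic analysis. What remains is that the protocol did not leave the matter open: it named a method for the results as a whole. When the committee asked for more detail on the analyses (8.5.2), the reply pointed to section 2.

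A second reply concerns which inputs are affected, and it is right. Disability weights do not drive the per-QALY curve, whose utilities come from the study's EQ-5D-5L. Unit costs rest on tariffs and should not be counted as literature estimates with sampling error.

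A third concerns size. The horizon, the coefficients of variation and the 95% threshold are not in the protocol, and 2.80 comes from a DALY power calculation, not from net benefit. A reader might take the 7–34% of Case B as the expected error. The documents do not support that, because they describe long-term consequences as partly study-based, which favours Case A. The appendix on efficiency gains also expects BETER care to be cheaper (€996 against €1,267 per patient per year). If it is, the Case A probability barely moves.

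**Conclusion.** The stated uncertainty method suits the 5-year result and does not suit the lifetime result. If section 2.4 is followed as written for both, the uncertainty of the literature inputs is missing from the lifetime intervals and curve. The direction follows from how the bootstrap works. The size cannot be derived from the documents.

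Under the multiplier assumption the distortion is modest: a false-reading rate of about 5–6% at a coefficient of variation of 0.1 and about 10% at 0.6, against 5%. It is larger if literature supplies the post-study benefit independently, and small for the curve if BETER care saves money. The stronger inference, that BETER care would be declared cost-effective with near certainty on inadequate evidence, goes beyond what the protocol shows. The section should be amended, but the 5-year analysis is not undermined.

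**What to change.** In section 2.4, tie the bootstrap sentence to the 5-year study-based analysis and add a paragraph for the lifetime model:

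- In each replicate, resample the study patients and also draw the uncertain literature inputs from distributions. Use the published standard error where there is one, and a stated plausible range otherwise.
- Treat disability weights this way for cost/DALY only. Tariff prices can stay fixed.
- Simulate enough patients per replicate to make Monte Carlo noise negligible.
- Build the lifetime intervals and acceptability curve from these replicates.
- Add scenarios for how long the effect lasts after follow-up.

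This needs one paragraph, some extra programming and more computing time, but no new data or patients. The price is wider lifetime intervals and a flatter lifetime curve.

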### 3. BUDGET IMPACT ANALYSIS (BIA)

#### 3.1. General considerations

A BIA will be performed to estimate the 5-year financial consequences of adoption and diffusion of the BETER care in the Dutch healthcare system. The following points will be addressed: the proposed intervention, the potential number of patients that are eligible for the intervention, costs per patient, treatments, palliative care. The guidelines from the Dutch Zorginstituut and ISPOR 2016 will be followed for the design and execution of the BIA.

#### 3.2. Cost Analysis

The costs gathered for the Cost-effectiveness analysis will be used applicable for the BIA.

### 4. SYSTEMATIC REVIEW

#### 4.1 Search Strategy

Publications about the effectiveness of survivorship care for survivors of HL or childhood cancer were identified by a structured search strategy. We searched the databases of Pubmed, Embase (Ovid) and Scopus for relevant publications till February 19, 2020. The search strategies that were used can be found in Supplement 6.

Although our project aims to evaluate the effectiveness of survivorship care for HL survivors, we also selected literature about the effectiveness of such care for childhood cancer survivors. This was done because we expected there would be very little literature on HL and possibly a bit more for childhood cancer, as the establishment of survivorship care for HL is quite recent, while such care for childhood cancer survivors has been initiated around 2005-2010. We assumed that results from studies in childhood cancer survivors could also be relevant for our research question.

To assess whether a publication was relevant we applied the following criteria:

1. The study should include screening (surveillance) for long-term adverse effects of cancer treatment;
2. The study population should consist of (at least) 5-year survivors of lymphoma or childhood cancer;
3. The studied intervention should be (one of) the screening methods/interventions used in BETER, i.e. screening and treatment for breast cancer, CVD, cardiovascular risk factors, thyroid dysfunction or vaccination for asplenia (spleen dysfunction);
4. The study should include a control group receiving usual care (or no care);
5. The outcome of the study should not (only) be the diagnostic accuracy of the screening method but (also) effectiveness and/or cost-effectiveness of the screening/survivorship care program;
6. The study outcome measure(s) should include one or more of our primary outcome measures: the burden of disease or yield of one or more late adverse cancer treatment effects, or health care costs;
7. The study outcome(s) should be assessed in clinical practice; therefore simulation studies modeling effectiveness of cancer survivor care programs based on a simulated cohort of cancer survivors or on data for other (non-cancer) high-risk groups were excluded.

#### 4.2. Results

639 titles were retrieved about survivorship care for HL survivors (315 from Pubmed, 194 from Embase(ovid) and 130 from SCOPUS) and 176 titles were retrieved for childhood cancer survivorship care (98 from Pubmed and 45 from Embase(ovid) and 33 from SCOPUS). After removing 269 duplicates, 546 publications were assessed for eligibility.

First, titles and abstracts of publications identified by the search strategy were independently screened by 2 reviewers ([name], [name]). Second, full-text papers of all selected publications were retrieved. Both reviewers independently assessed each retrieved full-text paper to determine whether it met the inclusion criteria.

Based on titles and abstracts, 31 titles were obtained in full text, 26 for HL and 5 for childhood cancer. If the 2 reviewers disagreed with respect to the eligibility of a title/abstract, we always obtained and assessed the full text. The most important reason for exclusion of titles was that studies only reported on the risk of long-term adverse events (recommending screening for late effects in their conclusion), but did not examine the effect of an intervention to reduce the risk. Other studies were excluded as they studied the diagnostic accuracy of screening interventions or studied screening interventions not (yet) part of the BETER screening program.

After closer inspection of the 31 publications obtained in full text, it turned out that none of the publications met the inclusion criteria. Most frequent reasons for ineligibility of papers were:

1. Description of screening program, no results;
2. Intervention did not correspond to (one of) the screening methods/interventions used in BETER survivorship care;
3. Simulation study, no data from clinical practice;
4. No comparison group;
5. Reported outcome measures did not correspond with one of the primary outcomes in our proposed study; e.g. only participation rates or diagnostic accuracy of one of the BETER screening methods were reported.

All publications obtained in full-text were hand-searched for additional relevant references; this yielded 8 potentially relevant papers.

We also searched ClinicalTrials.gov, a website which provides a worldwide overview of ongoing clinical studies that are currently recruiting patients and have not yet been published. This website is maintained by the National Library of Medicine and the National Institutes of Health and has information on publicly and privately supported clinical studies on a wide range of diseases and conditions. We did not identify any ongoing studies examining the effectiveness of survivorship care (or screening for late adverse effects) in survivors of HL or childhood cancer.

#### 4.3. Synthesis of evidence

##### 4.3.1. Signorelli et al. (2017)

The most promising publication was a systematic review published on the impact of long-term follow-up care for childhood cancer survivors by Signorelli et al. in 2017 (29). The authors assessed impact of engagement in specialized survivorship care on survivors' medical and psychosocial outcomes. Nine eligible articles were found. The majority of studies focused on knowledge about late effects (n=4), risk perception of late effects (n=4), general health care use and use of support services (n=4), and number of late effects detected (n=4; no comparison group).

Although none of the papers addressed the (cost-)effectiveness of survivorship care in terms of reduced morbidity and/or mortality from late effects, we briefly describe here the most important results of this systematic review. Survivors attending follow-up care tended to demonstrate higher knowledge about their treatment and diagnosis (n = 2), and had more accurate late effects risk perception (n = 3). Attendees engaged in increased more regular surveillance, had fewer emergency department visits/hospitalizations (n = 1), and more late effects detected (n = 3), than non-attendees. No significant differences were observed between attendees and non-attendees in psychological morbidities, including post-traumatic stress disorder

(30). Although not significant either, attendees tended to report higher distress levels than non-attendees. Survivors with moderate/severe late effects who were disengaged from follow-up, had significantly lower health-related quality of life than survivors under surveillance with no/mild late effects, worst on physical and social functioning, vitality and general health perceptions scales (31).

Signorelli and colleagues concluded that there is a dearth of literature systematically evaluating the medical and psychosocial impact of follow-up care.

We identified a few papers with results that had some relevance for our research questions, although none of them addressed the (cost-)effectiveness of survivorship care in terms of reduced morbidity and/or mortality from late effects. One of these papers was included in Signorelli et al, and two were not included as they concerned HL survivors. We briefly describe these papers below.

#### 4.3.2. Chen et al (2009)

Chen et al (2009) evaluated lipid screening and statin use in a hypothetical cohort of 30-year old 5-year HL survivors treated with chest radiation (13). They compared no screening with screening at 1-, 3-, 5-, or 7-year intervals and used Markov models to calculate life expectancy, quality-adjusted life expectancy and life-time costs. A 3-year interval was most cost-effective. The authors pointed out that their results were very sensitive to the assumptions made in the models regarding the magnitude of the risk increase of CVD in Hodgkin survivors and the efficacy of statin use in this specific population (unknown because of potential different pathogenesis of CVD).

#### 4.3.3. Furzer et al (2020)

Furzer et al (2020) used simulation models to evaluate the cost-utility of 8 different breast cancer screening strategies for adolescent HL survivors treated with chest radiotherapy, starting at 25 years of age (14). No comparison was made with no screening (i.e. no screening till the age of recommended population screening); the reference was annual MRI and mammography from age 25 (Childhood Oncology Group guideline). Among all assessed surveillance strategies, the differences in life expectancy were small, but annual MRI alone from age 25 was the most cost-effective strategy. In a previous simulation model, the same authors estimated that 80 patients would need to be invited to MRI-based screening to prevent one breast cancer death, indicating that MRI-based screening should reduce breast cancer mortality in young Hodgkin survivors (32). A limitation of these simulation analyses is that model assumptions about the efficacy of breast cancer screening at young ages were mostly based on BRCA1/2 mutation carriers, who are known to have different breast cancer tumor characteristics than other women.

